### 2.7. Statistical Analysis Plan

The descriptive results will be expressed as the means ± standard deviation, and 95% confidence intervals will be expressed as frequency distributions.

Generalized linear models (GLMs) will be used to analyze the differences between the intervention and control groups and changes in primary and secondary outcomes before and after the intervention and control group interventions. McNemar tests will be used to analyze changes at the primary outcomes in the intervention and control groups over time in the case of dichotomous categorical variables. The main analysis will be based on the Intention-To-Treat (ITT) population, and a sensitivity analysis based on multiple imputation [25] will be conducted for all variables. One hundred datasets with no missing values will be generated using the package mice [26] for software R version 3.3.3 (The R Foundation for Statistical Computing, Vienna, Austria) [27] with the appropriate approach depending on the nature of the variable.

To allow comparability between this study and previous literature, the main analyses will also be stratified by gender.

The significance level is fixed at a bilateral level of 5%. All statistical analyses will be performed with R software version 3.3.3 and SPSS version 23.00 (SPSS, Inc., IBM, Armonk, NY, USA).

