## Abstract

Introduction: The EYTO-kids (European Youth Tackling Obesity in Adolescents and Children) study aims to increase fruit and/or vegetable consumption and physical activity, decrease sedentary lifestyles, and reduce the intake of sugary drinks and fast food using an innovative methodology based on social marketing and youth involvement. Methods: This study is a pilot school-based cluster randomized controlled 10-month intervention spanning two academic years (2015–2016 and 2016–2017), with eight primary schools and three high schools randomized into and designated the control group and eight primary schools and four high schools designated the intervention group in Reus, Spain. At least 301 younger school peers per group should be included. At the intervention high schools, the adolescent creators (ACs) receive an initial 16-h training session. In total, 26–32 high school ACs (12–14 years) from the four high schools will design and implement four health-promotion activities (1 h/each) for their younger (8–10 years), primary school peers. The control group will not receive any intervention. The outcomes (fruit, vegetable, fast food and sugary drink consumption; physical activity; and sedentary behaviors) of the control and intervention groups will be measured pre- and post-intervention. Conclusion: This study describes a protocol for pilot, peer-led, social marketing and youth-involved intervention, where adolescents design and implement activities for their younger peers to promote healthy lifestyles.

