### 2.2. Study Design and Setting

The EYTO-kids project is a school-based pilot cluster randomized controlled intervention with a duration of 2 academic years (2015–2016 and 2016–2017) that is being conducted for 10 months in Reus, Spain. In Reus, 20 public primary schools and 8 high schools that serve low-income neighborhoods were identified. Of these schools, 4 public primary schools and 1 high school decided not to participate in this project. The randomization code was computer generated with Research Randomizer software (Geoffrey C. Urbaniak and Scott Plous, Lancaster, PA, USA) [20]. Furthermore, the unit responsible for the randomization was separate from the study researchers. Because the researchers knew the names of the schools, the allocation was not blinded. Then, the primary schools and high schools were assigned to the control or intervention arm at a ratio of 1:1 via an interactive electronic response system hosted by the Nutrition and Health Technology Centre (CTNS) in Reus, Spain. The unit responsible for the randomization will take no further part in the study. Because the researchers know the names of the 4 high schools, allocation concealment is not performed. The intervention group will receive the intervention; no intervention will be performed for the control group. An evaluation will be performed before and after the intervention in both participant groups (Figure 1). 

All participants will have informed consent forms signed by their parents or guardians. The EYTO-kids project has the approval of the Ethical Committee of the Hospital Universitari Sant Joan de Reus (ref: 16-01-28/1proj1), and the trial is registered with ClinicalTrials.gov (NCT02702336). The protocol is in accordance with the Helsinki Declaration and the Good Clinical Practice guidelines of the International Conference on Harmonization (ICH GCP). This randomized trial is being conducted according to CONSORT 2010 guidelines. Furthermore, this study adheres to the following Standard Protocol Items: Recommendations for Interventional Trials (SPIRIT) (Supplementary Materials 1) and Better reporting of interventions: template for intervention description and replication (TIDier) protocol guidelines (Supplementary Materials 2).

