-The ACs will design 4 activities based on the 8 SMBC and will be supervised by the physicians and nutritionists specializing in health education and promotion (6 h). The 26 ACs for each of the 4 intervention high schools will lead 4 activities involving healthy lifestyles, with a total of 104 ACs.-Exhibition of activities designed by the ACs for the ACs of the other high schools (2 h).-Standardization and training in each high school regarding the 4 activities designed by the ACs (6 h). The AC activities will be standardized with those of other high school ACs to accurately implement each activity in all of the primary school interventions. To achieve standardization, the activities will be written as theatre scripts, and the ACs will repeat the activities until all of the ACs transmit the same health message.-In groups of 2–6 ACs from the same high schools, the ACs will implement the activities designed for primary schools (4 h) according to Table 1.

In general, the ACs from four intervention high schools will implement the 4 activities for their younger school peers in 8 nearby primary schools as described in Figure 2.

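### Schools are randomised, but the analysis section names only methods that treat children as independent, so the stated 5% level is not controlled

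*Protocol article*

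**What the plan says.** Section 2.2 describes the trial as a "school-based pilot cluster randomized controlled intervention" and says that "the primary schools and high schools were assigned to the control or intervention arm at a ratio of 1:1". The Abstract gives the numbers of units: "eight primary schools and three high schools randomized into and designated the control group and eight primary schools and four high schools" in the control and intervention arms respectively. Section 2.4.2 adds a delivery layer above the primary school: "the ACs from four intervention high schools will implement the 4 activities for their younger school peers in 8 nearby primary schools".

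Section 2.7 names the methods. For the comparison between arms and for change: "Generalized linear models (GLMs) will be used to analyze the differences between the intervention and control groups and changes in primary and secondary outcomes". For change within each arm: "McNemar tests will be used to analyze changes at the primary outcomes in the intervention and control groups over time". The significance level is two-sided 5%. A multiple-imputation sensitivity analysis with 100 datasets is planned in the R package mice, "with the appropriate approach depending on the nature of the variable".

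Section 2.7 does not mention school. Neither section 2.6 nor section 2.7 gives an ICC or a design effect, and no other section supplies an adjustment for clustering.

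**The concern.** Children in one school share teachers and surroundings. In the intervention arm they also share the adolescents who deliver the activities. Their answers are therefore likely to be correlated, and the information on the effect of allocation comes from 16 schools, not from some 600 independent children. A model that counts each child as a separate randomised unit will usually understate the uncertainty of the difference between arms.

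At stake is the claim of effectiveness. The article states an effectiveness hypothesis and plans two-sided 5% testing of primary and secondary outcomes, so the pilot label does not remove the problem. A difference that merely reflects which schools fell into which arm could be reported as significant.

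**Working it through.** **Inputs from the article.** 8 primary schools per arm (Abstract); 301 children per arm and 30% loss (section 2.6); two-sided 5% (section 2.7). Whether 301 is before or after loss is not clear, so both are used:
- 301 / 8 = 37.6 children per school
- 301 × 0.7 ≈ 211, and 211 / 8 = 26.4 children per school

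**Assumed.** The ICC, over a range from 0.005 to 0.05, and equal school sizes.

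**1. Unadjusted comparison of post-intervention percentages.** Design effect DE = 1 + (m − 1) × ICC. The true standard error is √DE times the one used, so the actual level of a nominal 5% test is 2 × [1 − Φ(1.96 / √DE)]. At ICC = 0, DE = 1 and the plan's own 5% is recovered.

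| ICC | DE, m = 37.6 | SE ratio | Actual level | Actual level, m = 26.4 |
|---|---|---|---|---|
| 0.005 | 1.18 | 1.09 | 7.2% | 6.5% |
| 0.01 | 1.37 | 1.17 | 9.4% | 8.0% |
| 0.02 | 1.73 | 1.32 | 13.6% | 11.0% |
| 0.05 | 2.83 | 1.68 | 24.4% | 19.3% |

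Example: at ICC 0.02, DE = 1 + 36.6 × 0.02 = 1.73; 1.96 / 1.32 = 1.49; two-sided tail 13.6%. Beta-binomial simulation with 8 v 8 schools of 38 children agreed: about 7%, 9%, 13 to 14% and 24 to 25%. In the same kind of simulation a t-test on school percentages (8 v 8) held 4.9% to 5.1%.

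**2. Analyses of change.** Section 2.7 also covers change and does not fix the model form, so two forms are worked. Scale the outcome variance to 1. Let ρ be the correlation between a child's two records, and let s be the part of the ICC that is specific to one time point; the rest is stable and cancels from change. Take m = 38 and assume ρ = 0.34.
- *Group-by-time GLM with all records treated as independent:* ratio of true to assumed variance = (1 − ρ) + (m − 1)s.
- *GLM on each child's change:* ratio = 1 + (m − 1) × s / (1 − ρ).

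| ICC | s | Group-by-time: ratio, level | Child-level change: ratio, level |
|---|---|---|---|
| 0.02 | 0 (all stable) | 0.66, 1.6% | 1.00, 5.0% |
| 0.02 | 0.01 (half) | 1.03, 5.3% | 1.56, 11.7% |
| 0.02 | 0.02 (none stable) | 1.40, 9.8% | 2.12, 17.8% |
| 0.05 | 0.025 (half) | 1.585, 12.0% | 2.40, 20.6% |

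Simulation of the group-by-time form gave 1.5%, 5.0%, 9.8% and 12.1%. Ignoring the pairing makes the test too cautious, ignoring schools makes it too liberal, and the two errors may or may not offset each other.

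**3. McNemar within one arm.** Simulated with 8 schools of 38 children and an assumed 30% discordant pairs. The level was 5.0% with no between-school variation in change, 8.5% with a between-school SD of change of 0.05, and 18.8% with an SD of 0.10.

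**The case against.** The strongest reply is that the size of the problem is not a property of the plan. The article gives no ICC, the model form is open, and the figures in step 1 belong to a post-only comparison without baseline. This stands. A reader might infer that the test is far from 5% under any GLM that section 2.7 permits. The documents do not support that: step 2 shows a permitted reading with about 2% to 10% at ICC 0.02. The reply does not restore control of the error. A level that may be 2%, 5%, 10% or 18%, depending on unstated choices, is not a fixed 5%.

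Three further limits also stand.

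- **High-school catchments.** A reader might treat the four high schools as the real clusters, with about 75 children each, and quote about 22% at ICC 0.02. That needs four such clusters in both arms. The control arm has three high schools and receives no activities. With catchment clustering in the intervention arm only, the average DE is (2.48 + 1.73) / 2 = 2.11, and the level is about 17 to 18%.
- **Imputation.** A reader might infer that the imputation is single-level. The wording on the nature of the variable neither specifies nor excludes two-level methods, and imputation is only a sensitivity analysis here.
- **McNemar.** It tests change within one arm and is not the randomised comparison, so its error depends on between-school variation in change.

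It may also be said that a condensed article leaves such details to a full plan. That would excuse a missing small-sample correction, but not this gap. Section 2.7 is specific down to the number of imputed datasets and the software versions, and the methods it names do not match the design in section 2.2. Some software does offer GEE or mixed models under a generalized linear models label, but the text names no such extension, and a standard McNemar test has no place for school.

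**Conclusion.** The point holds. Section 2.7 specifies an individual-level analysis for a trial that randomises schools, and nothing elsewhere in the article repairs this, so the two-sided 5% level is not controlled.

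The firm part is the mismatch. The size is conditional. For an unadjusted post-intervention comparison with about 38 children per school, the error exceeds 5% at any positive ICC; it nearly doubles at 0.01 and is about five times nominal at 0.05. At 0.005 it is only mildly raised. For a GLM on child-level change, it is inflated unless school effects are fully stable over time. For a group-by-time GLM on unpaired records, the direction itself is uncertain. All of this rests on assumed ICCs, equal school sizes and, for change, an assumed within-child correlation of 0.34. The article asks for at least 301 children per arm; more children in the same schools would raise the design effect.

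Because it touches the primary and all secondary comparisons, it should be corrected before analysis.

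**What to change.** - **Main analysis.** In section 2.7, replace the unspecified GLMs by one cluster-aware model for primary and secondary outcomes: a mixed logistic model, or GEE with bias-corrected standard errors. Use post-intervention status as outcome, arm and baseline status as fixed effects, and primary school as the cluster. Use a small-sample reference of about 14 df (16 schools − 2 arms; critical value 2.14 in place of 1.96). A school-level analysis or a permutation test over schools is an acceptable alternative.
- **McNemar.** Report it as descriptive only, or replace it with a cluster-adjusted version.
- **Imputation.** State that school enters the imputation model, so that the sensitivity analysis matches the main analysis.
- **Shared delivery.** Add a sensitivity analysis that allows for delivery by the four intervention high schools, since 14 df may be optimistic if that layer matters.

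The cost is a change of wording, a little more analysis work in R, which is already planned, and somewhat wider confidence intervals. Recruitment and data collection are not affected.

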### 2.5. Primary and Secondary Outcomes

The expected primary outcomes are to increase the percentage of younger school peers who consume ≥1 fruit/day and practice ≥4 h/week of physical activity. The secondary outcomes are to increase the percentage of younger school peers who consume ≥1 vegetable/day and to decrease the percentage of younger school peers who have sedentary behaviors, consume a large number of sugary drinks/day and visit fast food restaurants more than once/week. 

To evaluate the primary and secondary outcomes, younger school peers from the intervention and control groups will answer a questionnaire before and after the control and intervention group interventions composed of 4 validated questionnaires:

(a) Fruit and vegetable consumption and fast food restaurant frequency: the EnKid questionnaire [21].

(b) Physical activity practice: the AVall questionnaire [22].

(c) Sedentary behavior (time spent watching TV or/and playing videogames and using the computer): the Health Behavior in School-aged Children (HBSC) questionnaire [23].

(d) Sugary drink consumption: the HABITS questionnaire [24].

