### 2.6. Sample Size

The sample size of this EYTO-kids project is calculated to detect a 5% rate difference among younger school peers who consume ≥1 fruit/day or practice ≥4 h/week of physical activity between the intervention and control groups. For an alpha risk of 0.05 and a beta risk of 0.1 in a bilateral comparison, 301 primary schoolchildren are required in the first group (intervention), and 301 are required in the second group (control). An estimated 30% rate loss takes into account the losses observed in the previously conducted EYTO study [19].

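### Between-arm GLMs and within-arm McNemar tests are both planned for the two primary outcomes, and the plan does not say which one decides effectiveness

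*Protocol article*

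**What the plan says.** Section 2.5 (Primary and Secondary Outcomes) defines the primary outcomes as percentages that should rise: "The expected primary outcomes are to increase the percentage of younger school peers who consume ≥1 fruit/day and practice ≥4 h/week of physical activity". Each is a yes/no variable per child, measured by questionnaire before and after the intervention in both groups.

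Section 2.7 (Statistical Analysis Plan) names two analyses for these outcomes:

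- First, "Generalized linear models (GLMs) will be used to analyze the differences between the intervention and control groups and changes in primary and secondary outcomes", comparing before with after.
- Then, "McNemar tests will be used to analyze changes at the primary outcomes in the intervention and control groups over time", limited to use "in the case of dichotomous categorical variables". Both primary outcomes meet that condition.

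The phrase main analysis is tied to a population only: "The main analysis will be based on the Intention-To-Treat (ITT) population". The section sets one two-sided 5% level for everything and gives no order of priority between the GLM and the McNemar tests.

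Section 2.6 (Sample Size) is built on a 5% rate difference between the intervention and control groups: "For an alpha risk of 0.05 and a beta risk of 0.1 in a bilateral comparison".

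**The concern.** A McNemar test within one arm asks whether the percentage changed between the two questionnaires in that arm. Ageing, season and familiarity with the questionnaire can all produce such a change, and they act in both arms. The test cannot separate them from the intervention; only the comparison with the control arm can. Finding significance in one arm and not in the other is not a test of the difference between arms.

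Two features of the text leave room for that misuse. The outcomes in Section 2.5 are worded as increases, with no reference to control, so a rise within the intervention arm would seem to satisfy them. The GLM sentence joins between-group differences and before-after changes, for primary and secondary outcomes together, without singling out one contrast. A report could therefore carry two kinds of result per primary outcome, with no prior statement of which one counts.

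The McNemar test also treats children as independent, whereas whole schools were randomised (Section 2.2). If schools differ in how much their pupils change, its p-value is too small.

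**Working it through.** **What is being checked.** The plan gives no error rate for this point, so there is none to reproduce. The 301 per arm in Section 2.6 is used here only as an input. It cannot be re-derived from the article, because no baseline rate is stated, and the argument does not depend on how it was obtained.

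**Which analysis addresses which question.**

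| Analysis | Question answered | Contrast sized in Section 2.6? |
|---|---|---|
| GLM, difference between groups | Do the arms differ? | Yes |
| GLM, before-after change | Depends on the term used | Not stated |
| McNemar in each arm | Did this arm change over time? | No |

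**Error rate if significance in the intervention arm alone were read as success.** This rule is hypothetical; the article does not state it.

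Inputs:
- n = 301 per arm (Section 2.6). It is unclear whether this is before or after the 30% loss; if before, 301 × 0.7 ≈ 211 remain.
- Two-sided 5% level, critical value 1.96 (Section 2.7).
- ψ, the share of children whose status changes in either direction: 0.30, assumed.
- d, the net rise common to both arms: 0 to 10 points, assumed.
- No intervention effect, and no clustering at this step.

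The probability that one arm shows a significant rise is

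π = Φ( (d − 1.96·√(ψ/n)) / √((ψ − d²)/n) ).

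With no intervention effect, both arms share the same π, so the probability of significance in the intervention arm only is π(1 − π).

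Example with d = 0.05 and n = 301: √(0.30/301) = 0.03157, and 1.96 × 0.03157 = 0.0619. √((0.30 − 0.0025)/301) = 0.03144. Then (0.05 − 0.0619)/0.03144 ≈ −0.38, π ≈ 0.353, and 0.353 × 0.647 ≈ 0.228.

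| Common trend | π (n = 301) | Intervention arm only, n = 301 | Same, n = 211 |
|---|---|---|---|
| 0 | 0.025 | 2.4% | 2.4% |
| 2.5 points | 0.121 | 10.6% | 8.8% |
| 5 points | 0.353 | 22.8% | 19.3% |
| 7.5 points | 0.663 | 22.4% | 25.0% |
| 10 points | 0.890 | 9.8% | 18.3% |

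Without clustering the ceiling is 0.5 × 0.5 = 25%, reached when each McNemar test has about 50% power.

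**Sensitivity to discordance.** Over the same non-zero trends at n = 301, 40% discordance gives about 9% to 25%. With 20% discordance the range is about 2.4% (at 10 points) to 25% (at 5 points). A large trend makes both arms significant and so lowers the figure.

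**Two primary outcomes.** If they are treated as independent, the chance of the pattern on at least one is 1 − (1 − p)². This is 1 − 0.976² ≈ 4.8% with no trend, and 1 − 0.75² ≈ 44% at the ceiling.

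**With variation between schools.** A simulation used 8 primary schools per arm, 30% discordance and a school-level SD of change of 0.10 (assumed). The pattern occurred in 8.6% of trials with no trend and in about 24% with a 5-point trend. A between-arm t-test on school mean changes stayed at about 5% two-sided, or about 2.5% in favour of the intervention.

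**The case against.** The strongest reply is that a between-arm analysis is planned, and it comes first. The GLM sentence directly precedes the McNemar sentence and covers the same outcomes. A GLM handles binary data, so nothing confines it to other variables. The sample size rests on the between-arm difference, which suggests that the GLM is meant as the test of effect and McNemar as a supplement. McNemar is assigned only to change over time, which is what it measures. This stands.

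A reader might therefore infer too much: that the primary outcomes are tested by McNemar alone, or that the plan lets the trial declare success with no intervention effect. The text supports neither reading. No section says that effectiveness will be judged from the McNemar tests, or from significance in one arm and not the other. The percentages above belong to a decision rule that the plan does not contain. They also depend on a trend and a discordance that the article does not give.

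It can also be said that model terms and the exact primary coefficient are normally left to a full analysis plan. That is true of the link function and the covariates. The point here concerns what the article does fix: two analyses of the same primary outcomes at the same 5% level, without priority, one of which is not a test of the intervention effect. Nothing in the text calls the McNemar tests supplementary or descriptive.

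**Conclusion.** The point holds as a lack of priority between two stated analyses. Section 2.7 specifies within-arm tests for both primary outcomes alongside a between-arm model and does not say which one decides. The within-arm tests do not address the contrast that the trial is sized for, and they ignore the randomisation by school.

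The size of the problem is conditional on how the results would be read. If significance in the intervention arm alone were taken as success, the false-positive chance per outcome would be about 2.4% with no common trend or clustering. That is no worse than a valid test in one direction. With a common trend of 2.5 to 10 points it would be about 10% to 25% (30% discordance, 301 per arm, no clustering). A common trend is plausible for a 10-month intervention spanning two academic years, but the article gives no figure for it. If the between-arm GLM is in fact the confirmatory analysis, none of this inflation arises and only the wording needs repair.

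**What to change.** Add a statement to Section 2.7 along these lines: for each primary outcome, the intervention effect is judged only from the between-arm contrast at follow-up, given as a risk difference or an odds ratio (one chosen in advance) with a 95% confidence interval. The model adjusts for the child's baseline status on that outcome and accounts for school, by a method suited to 8 primary schools per arm. The within-arm McNemar results are descriptive and do not bear on the conclusion about effectiveness.

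The cost is analysis wording. Baseline status and school are already recorded, so no new data are needed, and the McNemar tables can stay in the report under that label. The confirmatory analysis would then match the contrast on which Section 2.6 bases the sample size.

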## 2. Methods/Design

### 2.1. Study Aims 

The principal aims of this study are to increase fruit and/or vegetable consumption and extracurricular physical activity, decrease sedentary lifestyles and reduce the intake of sugary drinks and fast food using an innovative methodology based on social marketing and youth involvement. The project involves the design and implementation of health-promoting activities performed by adolescents and applied to their younger school peers. 

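### The success rule for the two primary outcomes is not fixed (*and* in 2.5, *or* in 2.6); if either one suffices at the undivided 5% level, the two-sided familywise error is up to 9.75%

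*Protocol article*

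**What the plan says.** Section 2.5 sets the primary outcomes: "The expected primary outcomes are to increase the percentage of younger school peers who consume ≥1 fruit/day and practice ≥4 h/week of physical activity". Vegetables, sedentary behaviour, sugary drinks and fast food are listed there as secondary.

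Section 2.6 gives the basis of the sample size. The trial "is calculated to detect a 5% rate difference among younger school peers" and the behaviours are then joined by *or*: "who consume ≥1 fruit/day or practice ≥4 h/week of physical activity". The error rates follow: "For an alpha risk of 0.05 and a beta risk of 0.1 in a bilateral comparison". The result is 301 children per group.

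Section 2.7 states that "The significance level is fixed at a bilateral level of 5" per cent. It gives no split, testing order or success rule for the two primary outcomes. Generalized linear models compare the groups, McNemar tests examine change within each arm on the primary outcomes, and "the main analyses will also be stratified by gender".

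**The concern.** With two primary outcomes, an overall 5% level has meaning only once the reader knows what counts as a positive trial. The two sections use different conjunctions for the same pair of behaviours, and each conjunction leads to a different statistical property:

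- **Either suffices.** Two chances at an undivided 5% exceed 5% overall.
- **Both required.** The 5% is safe, but the 90% power no longer describes the overall claim.

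So on either rule for two separate tests, one of the two error rates in 2.6 fails to carry over to the overall claim. While the rule is open, it can also be settled after the results are known. The hypothesis in the Background, that the activities would improve lifestyles, is loose enough for a win on one outcome to be presented as confirming it.

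**Working it through.** **Inputs.** Two primary outcomes (2.5); two-sided alpha 0.05, not divided (2.6 and 2.7); beta 0.1, so 90% power (2.6); 301 per group (2.6). The correlation between the two test statistics is not given, so a range is shown. Each single test is assumed to hold its own nominal level.

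**The plan's own figure.** The 301 cannot be reproduced from the stated inputs, because the control rate is not given. That is a separate matter. The 90% is taken below at its stated value, and every power figure is nominal in that sense.

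**Rule A: either outcome suffices**

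1. Independent tests, no true effect on either outcome: 1 − (1 − 0.05)² = 1 − 0.9025 = 9.75%.
2. Correlated test statistics (bivariate normal, both two-sided at 5%):

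| Correlation | Familywise error |
|---|---|
| 0 | 9.75% |
| 0.3 | 9.5% |
| 0.5 | 9.1% |
| 0.9 | 7.0% |

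3. False claims of benefit only, 2.5% per test under independence: 1 − (1 − 0.025)² = 1 − 0.950625 = 4.9%, against a nominal 2.5%.

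**Rule B: both outcomes required**

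1. No effect on either, independent: 0.05² = 0.25%.
2. A true effect on one outcome only: at most 5%, the level of the remaining test. Alpha is therefore held.
3. Joint power under independence, both effects real: 0.90² = 81%, so beta is 0.19 rather than 0.10. Positive correlation moves this towards 90% but does not reach it unless the two tests coincide.

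**Effect of correcting Rule A**

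1. At 2.5% per outcome, the familywise error under independence is 1 − 0.975² = 4.94%, and at most 0.025 + 0.025 = 5% under any correlation.
2. Power at the 2.5% step with N unchanged: Φ(1.960 + 1.282 − 2.241) = Φ(1.000) = 84.1%.
3. N needed to keep 90% at that step: [(2.241 + 1.282) / (1.960 + 1.282)]² = 1.18, so 301 becomes about 356 per group.

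**The case against.** The strongest reply is that the two sections do not conflict. The *and* in 2.5 may simply list two outcomes, and the *or* in 2.6 may mean that the same N was taken to serve each outcome singly. Neither sentence speaks of success, and 2.7 does not literally say that each outcome is tested at 5%. This stands in part: the either-suffices rule is an inference from the sizing sentence, so the 9.75% is conditional. But the benign reading still leaves two primary tests, one undivided level and no rule for combining them.

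A second reply is that a condensed article about a pilot may leave multiplicity to a fuller document. A bare omission could be excused that way. Here, however, the article states an alpha and a power and attaches them to an *or*, and its own analysis section repeats the undivided level. The pilot label does not change this, since 2.6 plans a two-sided comparison at 90% power.

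A third reply is that the outcomes are directional, so only false claims of benefit matter. Under independence that brings the absolute figure down to 4.9%, but the benchmark falls with it to 2.5%, and the near doubling remains.

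Two stronger readings are tempting, and the article does not support either:

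- A reader might count all the behaviours in 2.1 as primary, because they are called principal aims ("increase fruit and/or vegetable consumption and extracurricular physical activity, decrease sedentary lifestyles and reduce the intake of sugary drinks and fast food"). Section 2.5 expressly makes four of them secondary, and that section sets the hierarchy.
- A reader might count boys and girls as separate primary tests. Section 2.7 gives the purpose of the gender strata as comparability with earlier literature, and nothing makes a stratum result a primary claim.

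**Conclusion.** The point holds in conditional form. The success rule is not fixed, and neither rule for two separate tests lets the stated alpha and the stated power both apply to the overall claim.

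- If either outcome suffices, the two-sided familywise error is up to 9.75%, or about 7.0% to 9.5% for correlations of 0.9 down to 0.3.
- If both are required, there is no inflation, but joint power is about 81% under independence.

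A reader might infer that the trial's false-positive rate is simply close to 10%. The article does not support that without condition: the figure needs the either-suffices rule, near-independent tests, and significance in either direction counted as a claim. All figures assume that each test holds its own 5% and that 90% per outcome is correct as stated. The point deserves correction before analysis, and it does not by itself undermine the design.

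**What to change.** State one success rule and word it identically in 2.5 and 2.6.

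- **If either outcome suffices:** test the two between-group primary comparisons with Holm at a familywise 5% (the smaller p-value against 2.5%, then the other against 5%). Restate the power in 2.6 at 2.5%.
- **If both are required:** keep 5% for each and restate the joint power.

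In either case, say in 2.7 that the within-arm McNemar tests and the gender-stratified analyses are supportive and cannot establish the primary claim.

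The cost is mostly wording. Under Holm, nominal power per outcome at the first step falls from 90% to about 84% at the same N, or N rises by about 18% if 90% is to be kept at that step. If both are required, the cost is a less favourable stated power.
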